#### Primary Outcome

The primary outcome is maximal oxygen uptake (VO_2_max, mL·kg^−1^·min^−1^) measured at 24 weeks. VO_2_max is the criterion measure of maximal cardiorespiratory fitness [30], and an important clinical surrogate outcome as a 1 mL·kg^−1^·min^−1^ improvement has been associated with a 10% reduction in cardiovascular mortality among both men and women [50,51].

After a 5-min warm-up, an individualized treadmill cardiopulmonary exercise test is initiated at a self-selected velocity and 0% gradient. Thereafter, gradient is increased by 1% every 60 seconds until volitional exhaustion or indications for test termination [30]. A 5-min cooldown is completed at or below the self-selected velocity and 0% gradient. Cardiorespiratory responses are measured using a calibrated online metabolic cart; VO_2_max is defined as the mean value across 15 consecutive breaths before fatigue or symptom-limited test termination. Modification of treadmill velocity is permitted during the protocol if physiological responses indicate the self-selected velocity is insufficient to achieve an 8 to 12-min target test duration.

The individualized protocol is replicated at 24-week follow-up assessment; further modification of treadmill velocity is permitted after surpassing the baseline test duration, if required, to achieve a maximal performance.

Test procedures follow clinical guidelines, including continuous monitoring of 12-lead electrocardiogram, frequent assessment of blood pressure and patient-reported cardiovascular signs and symptoms, and medical support to administer treatment in the event of exercise-induced complications [30].

#### Secondary Outcomes

Secondary outcomes are outlined in Table 3. Resting systolic and diastolic blood pressure are measured after ≥10-min seated rest, in duplicate, to the nearest 1 mmHg, using a calibrated automated sphygmomanometer. A third measure is taken if duplicates differ by >10 mmHg; outcomes are recorded as the mean of the closest 2 measures.

Anthropometry outcomes are measured in duplicate with calibrated tools. Stature and body mass are measured to the nearest 0.1 cm and 0.1 kg, respectively. Third measures are taken if duplicates differ by >0.5 cm or >0.2 kg, respectively. Waist and hip circumferences are measured in duplicate to the nearest 0.1 cm at the levels of the umbilicus and the furthest posterior protrusion of the buttocks, respectively. Third measurements are taken if duplicates differ by >0.5 cm; all anthropometric outcomes are recorded as the mean of the closest 2 measures. Body mass index is calculated as weight (kg)/height (m)^2^. Waist-hip ratio is calculated as waist circumference (cm)/hip circumference (cm).

Blood lipid and glucose concentrations are measured via peripheral capillary blood samples using a calibrated point-of-care analyzer (Cholestech LDX, Abbott). Participants are asked to fast (no food or nonwater beverages) for at least 3 hours before the appointments and blood samples are drawn before the cardiopulmonary exercise test.

Self-management behaviors are measured using validated self-report instruments (Table 3), including physical activity (Godin Leisure-time Physical Activity Questionnaire) [42], dietary intake (automated self-administered 24-hour dietary assessment tool [ASA24]-Australia) [43-46], alcohol consumption (Alcohol Use Disorders Identification Test-C) [47], medication adherence (Medication Adherence Scale) [48], and health-related quality of life (Assessment of Quality of Life 8-dimension) [49]. The ASA24-Australia is a Web-based diet recall tool. Participants complete a Web-based recall for 1 calendar weekday within 3 days of assessment appointments; those who require help complete the recall with a researcher at assessment appointments or via telephone. Recalls are audited to identify possible misreporting and participants are asked to complete a new recall if misreporting is confirmed.

#### Economic Evaluation

Detailed methods for the economic evaluation will be described separately but, briefly, the evaluation will adopt a health care system and a limited societal perspective incorporating all health care costs subsidized by state and Commonwealth governments in Australia. Types and costs of inpatient and outpatient health care as well as dispensed medications will be estimated from self-reported adverse events, the Australian Government Medicare Benefits Schedule, and the Australian Government Pharmaceutical Benefits Schedule, respectively. Productivity loss will be measured by self-reported work absenteeism.

A preference index for the calculation of quality-adjusted life years (QALYs) will be derived from the 8-dimension Assessment of Quality of Life to assess cost per QALY for comparison with other programs. Incremental costs per unit increase in the primary (VO_2_max) and secondary outcomes will also be calculated. Extensive probabilistic uncertainty analysis will be undertaken in addition to the base case analysis.

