#### Control

Participants randomized to the control arm are advised to seek referral to usual care CR—as described above—if they wish to participate. No additional support is provided (Figure 1).

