### Maintenance Phase (Weeks 13-24)

#### Exercise Training

Participants continue to receive individualized and progressive exercise prescription during the maintenance phase; however, the format of supervision and coaching changes. Participants quantify their exercise performance using the SCRAM smartphone app and wearable sensor as per the intensive phase, but they no longer receive real-time supervision or coaching throughout training sessions. Instead, exercise physiologists provide individualized coaching feedback and update exercise prescription parameters during weekly telephone calls, based on assessment of participants’ exercise performance and goal achievement using retrospective review features of the Web app. Nonadherence (ie, absence of recorded data) initiates prompts from exercise physiologists to promote reengagement.

As per the intensive phase, participants use the smartphone app to self-monitor exercise performance (in real time during exercise and retrospectively afterward using automated graphing elements); set exercise goals and review goal achievement feedback (using automated graphing elements); and receive evidence- and theory-based behavioral support push notifications.

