#### Outcomes

Outcome measures and the assessment schedule are summarized in Table 3. 

Baseline and 24-week assessments are conducted at trial centers; 12-week assessments are conducted via telephone and internet survey. Furthermore, 12- and 24-week assessments are permitted ±2 weeks of the scheduled date to meet participant scheduling commitments. Participants who do not attend assessments are rescheduled for a second appointment; those who do not complete the 12-week assessment but do not withdraw their participation are contacted to complete the 24-week assessment. If participants cannot attend the 24-week assessment in person, self-report data may be collected via telephone and internet survey to minimize missing data.

Demographic and eHealth literacy data are collected at baseline to describe sample characteristics. Clinical data (diagnosis and treatment, hospitalization, and medication) are obtained with consent from hospital records, where possible. Self-reported adverse events are recorded and/or updated throughout the participation period as required.

**Table 3 table3:** Schedule of enrollment, treatments, and assessments.

Activity		Description		Weeks −4 to 0		Week 0		Week 12		Week 24	
Enrollment		Contact details, eligibility criteria, verbal consent for trial referral		Yes		N/A^a^		N/A		N/A	
Consent		Trial procedures, health care/medication utilization data release		N/A		Yes		N/A		N/A	
Allocation		Concealed centralized computer-based randomization		N/A		Yes		N/A		N/A	

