**Secondary outcomes**											
	Anthropometry		Body mass, body mass index, and waist and hip circumferences		N/A		Yes		N/A		Yes
	Blood lipid concentrations^c,d^		Total/high-density lipoprotein/low-density lipoprotein cholesterol, and triglyceride		N/A		Yes		N/A		Yes
	Blood glucose concentration^c,d^		≥3 hours fasted		N/A		Yes		N/A		Yes
	Blood pressure^c,d,e^		Automated sphygmomanometer		N/A		Yes		N/A		Yes
	Physical activity		Godin Leisure Time Physical Activity Questionnaire, % reporting leisure score index ≥ 14 units [42]		N/A		Yes		Yes		Yes
	Dietary intake		Automated self-administered 24-hour dietary assessment tool-Australia, dietary guideline index, and vegetable and discretionary food consumption [43-46]		N/A		Yes		Yes		Yes
	Alcohol consumption		3-item Alcohol Use Disorders Identification Test-C Questionnaire, % reporting ≤2 drinks/day [47]		N/A		Yes		Yes		Yes
	Medication adherence		4-item Medication Adherence Scale, % adherent (score=4) [48]		N/A		Yes		Yes		Yes
	Health-related quality of life		Assessment of Quality of Life 8-dimension, multiattribute utility score [49]		N/A		Yes		Yes		Yes
	Adverse events^f^		Self-reported changes to health status		N/A		Yes		Yes		Yes
Economic evaluation		Delivery, health care/medication use, and participant costs		N/A		N/A		N/A		Yes	
Process evaluation		Semistructured interviews; utilization data		N/A		N/A		N/A		Yes	

^a^Not applicable.

^b^VO_2_max: maximal aerobic exercise capacity.

^c^Measured after ≥3 hour fast.

^d^Measured before cardiopulmonary exercise test.

^e^Measured after ≥10 min of seated rest.

^f^Documented as required throughout the participation period.

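### Inpatient costs are taken from self-reported adverse events, and because staff contact differs greatly between unblinded arms, events and admissions risk being captured unequally.

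*Protocol article*

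**What the plan says.** Economic Evaluation lists three kinds of care and three sources in matching order. It begins "Types and costs of inpatient and outpatient health care as well as dispensed medications will be estimated from self-reported adverse events" and continues with the Medicare and pharmaceutical schedules. Inpatient use and cost thus come from self-reported adverse events, outpatient care from the Medicare schedule, and dispensed medications from the pharmaceutical schedule. The section adds that detailed economic methods will be described separately.

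Table 3 lists adverse events as a secondary outcome, described as "Self-reported changes to health status", scheduled at weeks 0, 12 and 24, with the footnote "Documented as required throughout the participation period". The Outcomes section repeats the rule: "Self-reported adverse events are recorded and/or updated throughout the participation period as required". Neither statement separates the arms. On the mode of assessment: "Baseline and 24-week assessments are conducted at trial centers; 12-week assessments are conducted via telephone and internet survey".

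Outcomes also names a second source for admissions: "Clinical data (diagnosis and treatment, hospitalization, and medication) are obtained with consent from hospital records, where possible". Table 3 and the ethics section show that consent is sought for release of health care and medication utilisation data.

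On contact with staff, the maintenance-phase text says that "exercise physiologists provide individualized coaching feedback and update exercise prescription parameters during weekly telephone calls". Of the control arm, the article says "No additional support is provided". The Blinding section states that participants cannot be blinded after randomisation.

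**The concern.** Recording events as they come to light gives equal capture only if both arms have a similar chance to bring them to light. Here one arm is in regular touch with health professionals for 24 weeks and the other is not. If more events are learned of in SCRAM, its adverse-event rate and inpatient cost will look higher than control's even when the true rates are equal.

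Two results are exposed. The first is the adverse-event comparison, which carries weight because the trial has no data safety monitoring board. The second is cost-effectiveness, which the Objectives make part of the hypothesis: the inpatient component feeds the numerator of cost per QALY. The planned probabilistic uncertainty analysis describes random uncertainty and would not by itself remove a systematic difference in capture. The primary outcome, VO2max measured by blinded assessors, is not affected.

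**Working it through.** The documents give no adverse-event rate, admission rate or unit cost, so there is no planned figure to reproduce. The check compares the stated rules, followed by an illustration of scale.

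**1. Source of inpatient cost.** Three care types, three sources and *respectively* leave one reading: inpatient care maps to self-reported adverse events. The hospital records named under Outcomes are not mentioned in the costing sentence.

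**2. Recording rule.** Identical in both arms: scheduled at weeks 0, 12 and 24, plus as needed between them.

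**3. Opportunity to report between scheduled assessments.**
- *SCRAM, weeks 1-12:* an induction call, and symptom data reviewed live by exercise physiologists when a session falls within operating hours. The initial prescription is 3 sessions a week; 3 × 12 = 36 sessions if that number were kept throughout. Not all need be monitored live, because participants self-monitor outside those hours.
- *SCRAM, weeks 13-24:* weekly calls, so 12. If recorded data stop, staff prompt the participant, so someone who is ill or in hospital may be contacted for that very reason.
- *Control:* no treatment contact is described after the advice to seek referral. A participant who misses week 12 is next approached at week 24.

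The rule is equal; the opportunity is not. The planned 20% loss to follow-up (0.20 × 110 = 22 per arm) adds to this. A SCRAM participant may have mentioned an event before being lost, whereas a control participant lost before week 12 may never have been asked.

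**4. Scale, under assumptions.** Let the observed risk be the true risk multiplied by the probability of capture. Assume the same true risk in both arms, capture of 95% in SCRAM, and capture of 90%, 80% or 70% in control. The true risk cancels in the ratio:
- 0.95 / 0.90 = 1.06
- 0.95 / 0.80 = 1.19
- 0.95 / 0.70 = 1.36

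With an assumed true risk of 20% and the planned 110 per arm, SCRAM shows 110 × 0.20 × 0.95 = 20.9 events on average:

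| Control capture | Control events | Risk difference | Chance of a falsely significant SCRAM excess |
|---|---|---|---|
| 90% | 19.8 | 0.19 − 0.18 = 0.01 | about 4% |
| 80% | 17.6 | 0.19 − 0.16 = 0.03 | about 8% |
| 70% | 15.4 | 0.19 − 0.14 = 0.05 | about 17% |

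The last column is the probability that a two-sided 5% test (normal approximation) favours control; with equal capture it would be 2.5%. For the last row: z = 0.05 / √((0.19 × 0.81 + 0.14 × 0.86) / 110) = 0.05 / 0.0499 = 1.00, and the probability that a standard normal falls below 1.00 − 1.96 is 0.17.

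Over true risks of 10% to 30%, the false risk difference runs from 0.5 points (0.10 × 0.05) to 7.5 points (0.30 × 0.25). If cost is assigned per reported admission, the inpatient component moves by the same ratio. The effect on cost per QALY cannot be worked out, because the inpatient share of total cost is not given.

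**The case against.** A reader might infer that events are gathered continuously in SCRAM and only at two visits in control. The documents do not say this. The rule is the same for both arms, and the week 12 assessment is by telephone and internet. The asymmetry is an inference from unequal contact.

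Nor does any text say that exercise physiologists record trial adverse events. Their contacts are described as serving coaching and prescription, and outcome assessors enter the data to maintain blinding. A route from coaching contact into the adverse-event data is plausible but not stated. This stands, and it is why the point is a risk and not a demonstrated bias.

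A large count of extra contacts, such as 60 monitored sessions, would also go too far. It needs 5 sessions a week from the start, whereas the article begins at 3 and reaches 3 to 5 by the end of week 12, and not every session falls within operating hours.

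Admissions are memorable and both arms are asked about events at weeks 12 and 24, so the gap for inpatient cost may be well below that for minor events. That also stands, although memory helps only when the participant is reached.

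Finally, detailed economic methods are deferred, and hospital records may be intended for use there. The deferral covers detail, but it does not withdraw the source that the article names for inpatient care. It would be too strong, however, to say that the trial relies on self-report alone, since records are obtained where possible. It would also be wrong to extend the point to outpatient or medication costs, which come from the schedules.

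**Conclusion.** The concern holds as a risk of unequal ascertainment. Three stated facts support it: inpatient use and cost are assigned to self-reported adverse events, participants are unblinded, and SCRAM participants have much more staff contact than controls. The likely direction is against SCRAM, on both adverse events and inpatient cost.

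The size is unknown. The apparent ratio of 1.06 to 1.36 is simply the ratio of assumed capture probabilities; it applies one gap to every kind of event and should not be read as an estimate. The documents do not establish that bias will occur or that the collection rule differs by arm. The point still merits a change, because the article names the more vulnerable source for inpatient care while the trial already obtains a less vulnerable one.

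**What to change.** In the statistical analysis plan and the separate economic methods:

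1. Identify and cost inpatient episodes in both arms from the consented hospital records and utilisation data over the same window, randomisation to week 24. Use self-report to flag episodes for checking and to cover admissions outside the record sources. Show the latter as a separate line, so that inpatient cost can be read with and without them.
2. Base the between-arm adverse-event comparison on events elicited with identical questions at weeks 12 and 24, plus record-confirmed hospitalisations.
3. List separately any events learned only through intervention contacts, so that they remain visible for safety but do not enter the comparison.

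The cost is record-checking work under consent already sought, and a few sentences of plan text. With 54 participants randomised by September 2019, the change could be made during recruitment. Coverage will be incomplete for admissions to other hospitals, since records are obtained only where possible. Stratified randomisation by centre should help to keep that gap similar between arms.

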#### Process Evaluation

Semistructured exit interviews are conducted to understand usability, acceptability, engagement, and satisfaction with the SCRAM and usual care CR treatments, respectively. SCRAM treatment fidelity is assessed via exercise session completion (determined from recorded exercise training data), self-reported compliance with behavioral notifications, and SCRAM platform usage metrics. Usual care treatment fidelity is assessed via self-reported uptake of standard CR services. Process data will be summarized using descriptive statistics (quantitative questions and analytics) and general inductive thematic analyses (open-ended questions). Interview data will be transcribed verbatim and analyzed using a general inductive thematic approach [52].

### Data Collection and Analysis

#### Data Collection and Management

Primary outcome assessors have previous experience with cardiopulmonary exercise testing, and all outcome assessors completed standardized training for required data collection protocols/methods to ensure consistency across all 3 trial centers.

Trial data are collected and managed using REDCap tools hosted at Deakin University [53,54]. REDCap is a secure, Web-based software platform designed to support data capture for research studies. Trial data are recorded directly into REDCap case record forms or, if required, on hard copy case record forms and transcribed into REDCap as soon as possible. Data entry is conducted by outcome assessors to maintain blinding. Validation rules (eg, range and completion checks) are prespecified in REDCap to identify inaccuracies and missing data; outcome assessors respond to queries as required. Hard copy corrections (if required) are initialed and dated by outcome assessors and transcribed into REDCap as soon as possible; REDCap data logging maintains an auditable record of all electronic data entries and corrections.

Electronic data are stored on a secure password-protected server; hard copy data are stored in secure filing cabinets at trial centers until they can be transferred to the coordinating trial center. Access to trial data is restricted to members of the research team. A data manager and individuals approved by the trial steering group retain access to data from all trial centers; however, outcome assessors can only access data for their individual trial center. Unique reidentifiable codes are used to anonymize trial data. Access to identifiable data is permitted for the purposes of contacting participants, verifying data entry, analysis, auditing, or other purposes approved by the Steering Group. There are no significant or uncertain risks of harm associated with the SCRAM intervention or usual care CR, and no interim analyses are planned. Accordingly, no data safety monitoring board has been established [55].

#### Statistical Analysis

Baseline characteristics will be summarized descriptively for the full sample and by treatment group. A linear regression model—adjusted for baseline values and stratification variables—will be fitted to assess the primary outcome. Primary analyses will be performed on the principle of intention to treat. Assuming there is a reasonable amount (>5%) of missing data, primary analyses will be conducted using multiple imputation, imputing all outcomes using a single (joint) imputation model. Imputation models will include participant age, sex, type of diagnosis (eg, angina, myocardial infarction, and coronary revascularization), in addition to any other covariates that appear to predict missingness. A per-protocol analysis will be conducted with complete cases to test the robustness of treatment effects under different assumptions. Preplanned subgroup analyses will be conducted to determine treatment effects by levels of treatment adherence, sex, and trial center (Figure 1). Secondary analyses will adjust the regression model for baseline prognostic factors, including age, sex, and employment status.

A similar approach will be used to assess continuous secondary outcomes (Table 3); logistic regression will be used for binary outcomes. Model-adjusted estimates and group differences will be reported with 95% CIs and probability values. All statistical tests will be 2-sided at α=.05. The biostatistician will remain blinded throughout the analysis of treatment effects. A detailed statistical analysis plan will be developed before the completion of data collection to guide analyses.

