#### Sample Size

Our previous noninferiority trial [10] indicates that 174 participants are required to detect a clinically meaningful between-group difference of 2.0 mL**·**kg^−1^**·**min^−1^ in VO_2_max (SD 6.75 mL**·**kg^−1^**·**min^−1^, r=0.80 between repeated measures, β=.9, and 2-sided α=.05). Allowing for 20% loss to follow-up (17% in our previous trial), a total of 220 participants are required to ensure equal numbers per treatment arm (ie, 110 per arm). Minimum detectable between-group differences in secondary outcomes at 24-week follow-up are summarized in Table 4.

**Table 4 table4:** Minimum detectable differences in secondary outcomes (assuming a total sample size of 220 participants [110 per treatment arm] and beta=.8).

Secondary outcome	Group difference	Data source
Total cholesterol concentration	0.24 mmol·L^−1^	Maddison et al [10]
Low-density lipoprotein cholesterol concentration	0.16 mmol·L^−1^	Maddison et al [10]
High-density lipoprotein cholesterol concentration	0.10 mmol·L^−1^	Maddison et al [10]
Triglyceride concentration	0.29 mmol·L^−1^	Maddison et al [10]
Glucose concentration	0.60 mmol·L^−1^	Maddison et al [10]
Physical activity leisure score index	17%	Dale et al [40]
Health-related quality of life	0.06 units	Richardson et al [56]
Medication adherence	19%	Thornley et al [57]
Systolic blood pressure	4.70 mmHg	Maddison et al [10]
Diastolic blood pressure	2.76 mmHg	Maddison et al [10]
Body mass	3.80 kg	Maddison et al [10]
Body mass Index	0.90 kg/m^2^	Maddison et al [10]
Waist circumference	2.60 cm	Maddison et al [10]
Hip circumference	1.80 cm	Maddison et al [10]
Alcohol consumption	21%	Dale et al [40]
Dietary guideline index	3.70 units	Livingstone and McNaughton [45]

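### The stated robustness check, a complete-case per-protocol analysis, drops everyone whose week-24 VO2max was imputed and so cannot test the missing-at-random assumption behind the primary analysis

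*Protocol article*

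**What the plan says.** All references are to the protocol article.

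- **Primary outcome.** Under Primary Outcome, VO2max is "measured at 24 weeks". Table 3 schedules the treadmill test at weeks 0 and 24 only. Under Outcomes, "12-week assessments are conducted via telephone and internet survey", so there is no interim VO2max.
- **People who cannot attend week 24.** Under Outcomes: "If participants cannot attend the 24-week assessment in person, self-report data may be collected via telephone and internet survey to minimize missing data". A maximal exercise test cannot be self-reported, so their primary outcome is missing.
- **Primary analysis.** Under Statistical Analysis: "Primary analyses will be performed on the principle of intention to treat". The model is a linear regression "adjusted for baseline values and stratification variables". If more than 5% of data are missing, all outcomes are imputed together in one joint model. The named covariates are age, sex and diagnosis, plus anything that appears to predict missingness. Treatment arm is not named.
- **Robustness check.** The same section says: "A per-protocol analysis will be conducted with complete cases to test the robustness of treatment effects under different assumptions". The other listed analyses are subgroups by adherence, sex and center, and adjustment for prognostic factors. They are not presented as checks on missing data.
- **Expected loss and nonadherence.** Sample Size allows for 20% loss, against 17% in the sponsor's earlier trial. The maintenance-phase Exercise Training section foresees some disengagement: "Nonadherence (ie, absence of recorded data) initiates prompts from exercise physiologists to promote reengagement".

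**The concern.** Multiple imputation as described assumes that a participant without a week-24 test resembles retested participants with the same measured data. The natural question for a sensitivity analysis is what happens if that is false.

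The stated check does not ask it. Restricting to complete cases removes exactly those whose values were imputed. The per-protocol restriction then also removes retested participants who did not adhere. The analysis set moves closer to completers, although the stated aim is to vary the assumptions.

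This trial is exposed because stopping exercise and missing a maximal exercise test are plausibly linked. SCRAM is also the only program the trial itself delivers; usual care cardiac rehabilitation is self-initiated and provided elsewhere. If the imputed analysis and the per-protocol analysis agree, a reader will take this as robustness, yet neither has varied the assumption in doubt. VO2max also enters the planned incremental cost per unit of outcome, so its size matters beyond the significance test.

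**Working it through.** **1. Reproduce the plan's sample size.** Inputs from Sample Size: difference 2.0, SD 6.75, r = 0.80, two-sided alpha 0.05, power 0.90 (printed as a beta of .9).

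- Residual SD after baseline adjustment = 6.75 × sqrt(1 − 0.80²) = 6.75 × 0.6 = 4.05.
- n per arm = 2 × (1.960 + 1.282)² × 4.05² / 2.0² ≈ 86.2, rounded up to 87; total 174, as stated.
- 174 / 0.8 = 217.5, so 218, against 220 stated. The inputs are sound.

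**2. Standard error with 20% loss.** 220 × 0.8 = 176, or 88 per arm. SE = 4.05 × sqrt(2/88) = 0.61.

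**3. Limiting case.** Assume retested SCRAM participants gain 2.0 over control, SCRAM dropouts gain nothing over control, and control dropouts resemble retested controls. The true intention-to-treat effect is (1 − d) × 2.0, where d is the SCRAM loss:

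- d = 0.17: 1.66 (overstated by 0.34, ratio 1.20)
- d = 0.20: 1.60 (overstated by 0.40, ratio 1.25)
- d = 0.30: 1.40 (overstated by 0.60, ratio 1.43)

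**4. What each analysis would report.** Simulation of 600 trials with 110 per arm under the assumptions of step 3. The imputation model held only baseline VO2max, with or without arm, and no auxiliary data. For the per-protocol set, 80% of retested SCRAM participants were assumed adherent, unrelated to their gain.

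| Loss, control/SCRAM | Truth | Imputation with arm | Per-protocol complete-case | Jump-to-reference | Imputation without arm |
|---|---|---|---|---|---|
| 17%/17% | 1.65 | 2.00 | 2.00 | 1.66 | 1.66 |
| 20%/20% | 1.62 | 2.03 | 2.02 | 1.62 | 1.62 |
| 10%/30% | 1.37 | 1.95 | 1.96 | 1.37 | 1.54 |

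With arm in the model, the planned check agrees with the overstated primary result. Jump-to-reference shows the gap, as it should in a scenario built on its own assumption. The last column does not support leaving arm out: it pulls the estimate toward zero however the dropouts fared, and in the third row it misses the truth.

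**5. Where significance would be lost.** Shifting imputed SCRAM values by δ moves an estimate of 2.0 to 2.0 + d × δ. Holding the SE at 0.61 (half-width 1.96 × 0.61 = 1.20), the interval reaches zero when |δ| = (2.0 − 1.20)/d:

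- d = 0.20: about 4.0
- d = 0.17: about 4.7

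At d = 0.20, δ = −2 gives 1.6 (95% CI 0.40 to 2.80), still clear of zero, and δ = −5 gives 1.0 (−0.20 to 2.20). A range stopping at −2 would never reach the tipping point at the planned effect.

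**The case against.** **The SAP is not shown.** The article promises a detailed plan before data collection ends, and missing-not-at-random analyses are commonly left to it. A reader might infer that no such analysis will be done and that a bias would go undetected. The documents do not support that. What stands is narrower: the article itself names one check and says what it is for, and that check cannot serve as a test of the missing-data assumption.

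**The per-protocol analysis may be meant for adherence.** The text does not say that it is aimed at people who were not retested. This is fair, and it is a reason to keep the analysis. But the sentence directly follows the imputation plan, specifies complete cases and claims to vary the assumptions, so it will be read as covering missing data.

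**The imputation may do better than step 4.** The joint model includes self-reported outcomes from weeks 12 and 24. Covariates that predict missingness may be added, and session completion and platform use are recorded. For participants who stay in contact, part of the gap could be recovered. For those who cease all contact, little can be.

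**Direction is assumed.** Control participants can also start and abandon usual care rehabilitation, SCRAM participants may use it too, and medical reasons for missing a test arise in both arms. A participant may also miss week 24 after completing the 12-week intensive phase and keep some gain. No figure in the article shows that SCRAM dropouts fare worse. All of this stands, and it makes the bias conditional.

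**Conclusion.** The point holds in a limited form. The complete-case per-protocol analysis cannot test the missing-at-random assumption, because it excludes everyone to whom that assumption applies. This follows from the design and needs no numerical assumption.

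The overstatement is a possibility, not a finding. It needs arm in the imputation model (normal practice, but not stated). It also needs SCRAM participants who are not retested to fall short of similar retested ones by more than any matching shortfall among control dropouts. If none of the benefit is kept and auxiliary data recover nothing, about 2.0 would be reported where the truth is 1.66 (17% loss) or 1.60 (20% loss). Those are upper figures for equal loss in the two arms; partial retention gives less.

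The consequence is mainly one of size: the true effect would lie below the 2.0 that the plan calls clinically meaningful. A reader might infer that the trial's power falls from 90% to about 75%, from 1.6/0.61 = 2.62 and Φ(2.62 − 1.96) ≈ 0.75. That is not the rejection rate of the planned analysis, which in this scenario still estimates about 2.0. Losing significance would require SCRAM dropouts to be about 4.0 to 4.7 mL/kg/min worse than imputed.

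**What to change.** - Keep the per-protocol analysis as a supplementary analysis of adherence, and stop presenting it as the check on missing data.
- Add two sensitivity analyses on all randomized participants: (1) jump-to-reference imputation from the control arm for SCRAM participants with no week-24 VO2max; (2) a delta-adjusted tipping-point analysis shifting imputed SCRAM values from 0 to about −5 mL/kg/min, also allowing a shift in control.
- State that treatment arm is in the imputation model, and use the self-report and platform session data already collected as auxiliary variables. Session data exist only for SCRAM, so they have to enter in an arm-specific way.

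The cost is a few sentences in the SAP, which was still to be written at publication, and some programming. No new data collection is needed. The downside is that the sensitivity estimates may be less favourable than the primary one. Jump-to-reference is deliberately pessimistic for participants who trained for most of the program, and the delta analysis shows the ground in between.
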